## Methods

### Study design

The research project uses a pragmatic prospective longitudinal cohort design with two initial treatment arms: a weighted blanket intervention and standard melatonin treatment. Treatment selection will be based on family preference and clinical decision-making in routine clinical practice rather than randomization. Child-parent dyads will be followed from baseline to 12 months, with annual long-term follow-ups for an additional nine years. The rationale for the long-term follow-up is to capture children’s development from childhood through adolescence and into young adulthood. The main evaluation of real-world changes in sleep, treatment adherence, health-related outcomes and resource utilization will focus on the first 12 months after inclusion, whereas the annual long-term follow-ups will be exploratory and used to describe longer-term patterns of treatment use, adherence, treatment changes, sleep, health-related outcomes, and resource utilization. Treatment changes may include continued use, discontinuation, switching between treatments, and combined use of weighted blankets and melatonin. The cohort study is combined with a process evaluation and uses a hybrid type 1 effectiveness–implementation approach [32, 33], in which clinical outcomes are the primary focus and implementation outcomes and contextual determinants are explored in parallel. Quantitative, qualitative, and mixed methods will be used.

### Patient and public involvement

The research project has been planned in collaboration with the Child and Adolescent Mental Health Service (CAMHS) and its ADHD subunit in Region Halland in terms of recruitment (inclusion and exclusion criteria and process and workflow of recruitment), preparation of intervention, and selection of outcome variables. Moreover, because the project has an implementation focus, emphasis has been placed on finding solutions that are adapted to clinical practice and to do so in coproduction with clinical staff.

Apart from disseminating results through scientific peer-reviewed articles within the research community, the findings from the research project will be disseminated through popular science reports, clinical conferences, and communication, with a special focus on patient organizations, healthcare organizations, and national and regional policymakers.

### Participants and recruitment

Children aged 6–14 who are diagnosed with ADHD (according to the Diagnostic and Statistical Manual of Mental Disorders [DSM], Fifth Edition) [34], screen positive for sleep problems, and are patients at the ADHD unit at CAMHS in the south-west of Sweden are eligible for inclusion in the research project. Children with presumed uncomplicated ADHD are triaged to the ADHD unit, whereas children with significant comorbidity or complex psychosocial needs requiring more intensive care are referred to regular CAMHS outpatient care and are not eligible for inclusion [35]. Approximately 350 children with presumed uncomplicated ADHD are seen annually at the ADHD unit, and based on clinical estimates, approximately half of them, about 175 children per year, are expected to screen positive for sleep problems and therefore be potentially eligible for the study. Children, and one of their parents, will be asked to participate in the research project. At inclusion, participants will enter one of two initial treatment arms based on family preference and clinical decision-making: a weighted blanket intervention or standard treatment with melatonin. Recruitment of child-parent dyads is expected to continue until approximately 150 children have been enrolled in each of the weighted blanket intervention and standard melatonin treatment groups.

When families first seek treatment for their child at CAMHS, they have a short telephone interview as part of a structured triage. After triage, the children see a physician for assessment and care planning. If applicable, ADHD medication is also prescribed. At this visit, children and parents receive verbal and written information about the research project and are given a sleep problems screening form to fill out and bring to the follow-up visit.

The sleep problems screening form is completed by parents and consists of three items from the Swedish version of the Children’s Sleep Habits Questionnaire (CSHQ-SWE) [36, 37]. Each item is scored in terms of 0–1, 2–4, or 5–7 days per week. The items are: “Child falls asleep within 20 minutes after going to bed” (scoring criteria 0–1 or 2–4 days per week), “Child sleeps too little” (scoring criteria 2–4 or 5–7 days per week), and “Child awakes more than once during the night” (scoring criteria 2–4 or 5–7 days per week). Each item contains the follow-up question: “Is this a problem?” (yes / no). If at least one of the items fulfills the scoring criteria and is indicated to be a problem, the child is considered eligible for inclusion.

At the follow-up visit, the sleep problems screening form is assessed by a nurse. If the child fulfills the inclusion criteria of ADHD diagnosis, sleep problems, age 6–14 years, and is a patient at the ADHD unit, and if the child-parent dyad understands written and spoken Swedish, the child-parent dyad is invited to participate in the research project.

Recruitment to the research project will occur continuously and include both newly and previously diagnosed children at the unit, and those who use and do not use ADHD medication. Participants will enter one of two initial treatment arms: (1) weighted blanket or (2) standard treatment with melatonin. During follow-up, participants may continue their initial treatment, discontinue treatment, switch between weighted blanket and melatonin treatment, or use the two treatments in combination, based on family preference and clinical decision-making. Treatment use and treatment changes over time will be documented as part of the pragmatic evaluation.

Follow-up by healthcare professionals at the ADHD unit will be integrated into the standardized care pathway. At inclusion, they will provide information on available treatment options and support families in initiating the selected treatment. During follow-up, healthcare professionals will discuss treatment use, perceived effects, adherence, and possible difficulties. Decisions about treatment continuation, switching, or combined use of weighted blankets and melatonin will be made in dialogue between the family and healthcare professionals as part of routine clinical practice. The standardized care plan for this group is the following: Parents and adolescents aged 15 years or older are offered a one-day course about ADHD. During the first year, follow-up visits are scheduled four weeks after initiation of new medication, and after six months, regardless of medication use. After the first year, the minimum follow-up is a yearly visit up to age 18, with an additional visit if a new medication is introduced. Any anxiety or depressive episodes will be referred to primary psychiatric care up to age 18 years. More complicated psychiatric issues will be referred to the specialized child and adolescent psychiatric services within the same provider. After age 18, the care will be referred to adult psychiatry. If medication is discontinued for more than one year, regular contact with the unit will end, but care can be reinitiated if needed.

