## Background

Attention-deficit/hyperactivity disorder (ADHD) is a neurodevelopmental condition that involves difficulties with concentration, hyperactivity and impulsivity [1–3]. It affects 6–8% of children [4] and is twice as common among boys as it is among girls (10% vs. 5%) [5]. ADHD negatively affects health-related quality of life [6], school performance [7], and family life [8], and entails significant costs to society [9]. Among children with ADHD, up to 73% experience sleep problems [10], compared to 23% of healthy peers [11], with a higher prevalence among girls than boys (75% vs. 53%) [12]. Sleep problems may be transient, but approximately 10% have persistent problems lasting more than one year [13]. Common sleep problems are bedtime resistance, difficulties falling asleep, nightly awakenings, difficulties with morning awakenings, reduced sleep efficiency, and reduced total sleep time [14, 15], which may lead to daytime sleepiness [16, 17] and negative impact on quality of life, social functioning [16], and ADHD symptoms [15]. Sleep problems in this population also impact negatively on parental mental health [18]. To alleviate ADHD symptoms and facilitate everyday life, children are often treated with stimulants, which can induce or exacerbate sleep problems, such as insomnia [2].

Sleep problems can be treated pharmacologically and/or non-pharmacologically. Prescription of the pharmacological treatment melatonin has increased significantly in Sweden in recent decades [19], and about one third of children with ADHD in Sweden are prescribed sleep medication [20]. Melatonin has demonstrated safety and effectiveness, but side effects such as headache, nausea and fatigue have been reported [21] and long-term effects are insufficiently described. Many parents prefer non-pharmacological treatments to pharmacological treatments [22]. Non-pharmacological treatments commonly include interventions targeted at sleep hygiene, behavioral therapy or sensory aids, such as weighted blankets [23]. Weighted blankets have long been used as a complement to or replacement for pharmacological treatment for children with ADHD and sleep problems [24]. Although widely used in clinical practice, the effects of sleep interventions with weighted blankets have been sparsely studied [25].

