In 2020, because of a lack of evidence of their effectiveness, the Medical Technology Product Council in Sweden recommended that weighted blankets for sleep problems should only be prescribed in research studies. This recommendation was then included in the updated treatment guidelines published by the Swedish National Board of Health and Welfare in 2024 [26]. During the same period, our research group conducted a randomized controlled trial in which weighted blankets were compared with lighter control blankets in children with ADHD and sleep problems [27, 28]. Sleep was evaluated both objectively and subjectively by sleep actigraphy, questionnaires, and interviews [27, 29, 30]. Weighted blankets were found to increase total sleep time (mean difference 7.72 min) and sleep efficiency (mean difference 0.82%) and reduce nightly awakenings (mean difference − 2.79 min) and perceived sleep problems compared with the lighter control blankets. They were particularly effective for children 11–14 years of age with the inattentive subtype of ADHD. Results from sleep actigraphy did not support any changes in sleep onset [27]. The children experienced that the weighted blanket required adjustment to individual needs and preferences and adaptation to the environment, improved their ability to regulate worry and anxiety, changed sleep patterns, and promoted functioning in everyday life [29]. Parents experienced improved sleep routines, faster sleep onset, fewer awakenings, and increased well-being in their children, which in turn improved the children’s ability to manage school, leisure activities, and family life [30].

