### Data collection and assessment

The child-parent dyads answer individual questionnaires at baseline (before the intervention starts), at 1-, 3-, and 6-month follow-ups, at 1-year follow-up, and then annually for an additional nine years. Parent-reported measures include both parent self-reports and parent proxy-reports concerning the child. The questionnaires contain questions about sleep problems, everyday function, lifestyle habits, worry and anxiety, ADHD-related symptoms, health-related quality of life, pain, resource utilization, and questions related to the intervention (Table 1). A purposive sample of approximately 20–25 child-parent dyads from each treatment arm will be interviewed individually at 6 and 12 months.

The implementation of the intervention will be evaluated by resource utilization and interviews. Approximately 5–10 individuals from the clinical staff at the ADHD unit will be interviewed individually and/or in focus groups at 6 and 12 months.

**Table 1 Tab1:** Overview of outcome measures

		Child-reported measures	Parent-reported measures	Clinical staff–reported measures
**Sociodemographic variables**			Children: age, gender, country of birth, medical information, siblings, and age of siblings *. Parents: age, gender, country of birth, civil status, educational level, and employment. Partners: age, country of birth, educational level, and employment.	
**Primary outcomes**	Sleep problems		Children’s Sleep Habits Questionnaire (CSHQ) [36, 37] *, **	
	Treatment adherence and treatment changes		Usage of weighted blanket and/or melatonin *	
**Additional sleep-related measures**	Sleep problems	Insomnia Severity Index (ISI) [40] Sleep Self-Report (SSR) [41, 42]	Pediatric Insomnia Severity Index (PISI) [43] *	
**Secondary outcomes**	Everyday function	Child Outcome Rating Scale (CORS) [44] Work and Social Adjustment Scale, Youth version (WSAS-Y) [45]	Outcome Rating Scale (ORS) [46] Work and Social Adjustment Scale, parent version (WSAS-P) [45] * The Brief Child and Family Phone Interview (BCFPI) [47, 48] *	
	Lifestyle habits		Dietary habits, physical activity, screen time and sedentary time (Health Behaviour in School-aged Children (HBSC) survey) [49] *	
	Worry and anxiety	The State-Trait Anxiety Inventory – short form (Short STAI) [50–52]		
	ADHD-related symptoms		The Swanson, Nolan, and Pelham Scale (SNAP-IV parent) [53, 54] *	
	Health-related quality of life	EQ-5D-Y-3 L [55, 56]	EQ-5D-3 L [57, 58]	

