#### Sociodemographic variables

Parents will be asked to report their gender (man/woman/prefer not to say), child’s gender (boy/girl/prefer not to say), age, child’s age, civil status (single/spouse or partner), partner age, birth country, birth country of child, birth country of partner, highest educational level achieved (compulsory school/upper secondary school/university or college), partner’s highest educational level achieved, employment status (full time/part time/unemployment/parental leave/studies/sick leave or sickness benefit/other), partner’s employment status, number of siblings, and sibling(s’) age(s). Parents also report child comorbidity (no/yes and diagnoses), child medication (no/yes and type of medicines), child’s need for sleep medication (no/yes), and completion of treatment for sleep problems for the child during the last month (no/yes and type of treatment). An open-ended question enabling additional important information to be communicated is also included.

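### Stated eligibility does not address current or recent melatonin or blanket use, and prior sleep treatment, though recorded at baseline, is missing from the 12-month across-arm analysis

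*Protocol article*

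**What the plan says.** Participants and recruitment gives the conditions for invitation as "inclusion criteria of ADHD diagnosis, sleep problems, age 6–14 years, and is a patient at the ADHD unit", together with understanding of written and spoken Swedish. The only exclusion stated there is at triage: "children with significant comorbidity or complex psychosocial needs requiring more intensive care are referred to regular CAMHS outpatient care and are not eligible for inclusion". Recruitment is to "include both newly and previously diagnosed children at the unit, and those who use and do not use ADHD medication", which settles the position on ADHD medication but not on sleep treatment.

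The Background section gives reasons to expect some prior use. It reports that "about one third of children with ADHD in Sweden are prescribed sleep medication" and that "Weighted blankets have long been used as a complement to or replacement for pharmacological treatment for children with ADHD and sleep problems". It also reports a 2020 national recommendation, which "recommended that weighted blankets for sleep problems should only be prescribed in research studies".

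On timing, Data collection and assessment states: "The child-parent dyads answer individual questionnaires at baseline (before the intervention starts"; the abstract says the same in similar terms. Participants and recruitment has staff help families initiate the treatment they select, and the Intervention section describes melatonin by a starting dose and a range.

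Under Sociodemographic variables, parents report the child's medication and its type, need for sleep medication, and "completion of treatment for sleep problems for the child during the last month (no/yes and type of treatment". Under School absence and healthcare consumption, prescribed pharmacological treatment is taken from the health records.

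The quantitative methods name four covariates, to be used when appropriate: age, sex, ADHD medication and level of ADHD symptoms. Patterns of treatment use are to be taken into account in the long-term follow-up analyses.

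**The concern.** Arms are formed by family preference and clinical decision, not by randomization. What a child has already tried for sleep is an obvious influence on that choice. A family whose child still sleeps badly on melatonin may turn to the blanket, and a family content with melatonin may stay with it. Prior treatment also bears on how much the CSHQ score can still change. A variable related to both arm and outcome is a confounder, and this one is closer to the exposure than any of the four covariates named.

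Two things are at stake in the main 12-month evaluation. First, a child already using the arm's treatment may show less change from baseline than a new starter, which dilutes the change within the arm and distorts the contrast if such children are unevenly spread. Second, a child on melatonin who enters the blanket arm and continues melatonin is on both treatments from day 0. The plan describes combined use as something that arises during follow-up and gives this child no stated classification.

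**Working it through.** **The plan's own figure.** Inputs from Statistical power: baseline mean 53, assumed follow-up means 47 (blanket) and 43 (melatonin), common SD 8, two-sided alpha 0.05, power 80%. The difference is 47 − 43 = 4, so d = 4/8 = 0.50. By the normal approximation, n = 2 × (1.960 + 0.842)² × (8/4)² = 62.8, so 63 per group. The t-based solution is 63.77, so 64. The stated 64 reproduces. At the planned 150 per arm, power for 4 points is about 99%.

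The implied changes from baseline are 53 − 47 = 6 and 53 − 43 = 10.

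**Illustration of prior use.** The share p of prior users in this cohort is not given, so it is an assumption, shown over a range. I also assume that a prior user of the arm's own treatment enters at the same mean of 53 and gains nothing further, and I hold the SD at 8. Power is Φ(Δ / (8√(2/n)) − 1.96), with n = 150 per arm and 8√(2/150) = 0.924.

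*Same share in both arms:* Δ = 10(1 − p) − 6(1 − p) = 4(1 − p).

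*Melatonin arm only:* Δ = 10(1 − p) − 6.

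| p | Both arms: Δ | Power | Melatonin arm only: Δ | Power |
|---|---|---|---|---|
| 0 | 4.0 | 99% | 4.0 | 99% |
| 10% | 3.6 | 97% | 3.0 | 90% |
| 20% | 3.2 | 93% | 2.0 | 58% |
| one third | 2.67 | 82% | 0.67 | 11% |

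For one third in both arms: 10 × 2/3 = 6.67, 6 × 2/3 = 4.0, difference 2.67. For 10% in the melatonin arm only: 10 × 0.9 = 9.0, and 9.0 − 6 = 3.0.

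The left half of the table is dilution. The right half is bias from imbalance, which a larger sample would not remove. Earlier melatonin non-responders who choose the blanket could hold back that arm's change and push the contrast the other way. The documents give nothing from which to quantify this.

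**What adjustment can and cannot do.** A prior-use covariate removes the effect of imbalance between arms. It does not restore the new-starter contrast when prior users in both arms gain nothing further: the adjusted contrast then still averages 4 points in starters with 0 in the others. That is the reason for a separate analysis in new starters.

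**Size of the new-starter set.** If one third are prior users, 150 × 2/3 = 100 per arm remain. Then 8√(2/100) = 1.131, 4/1.131 = 3.54, 3.54 − 1.96 = 1.58, and power is about 94% before attrition.

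**The case against.** A reader might infer that baseline is simply not pre-treatment. The document does not support that. Both timing statements place baseline before treatment starts, staff help families to initiate treatment, and melatonin is described as starting. The arm's treatment is evidently meant to be new. What stands is narrower: nothing in the displayed criteria secures it, and starting one treatment does not rule out already using the other.

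A reader might also take the melatonin advantage to shrink to 0.67 points. That needs a one-third share in the melatonin arm, no further gain at all, and an unaffected blanket arm. The one-third figure is national, concerns sleep medication in general, and is not this cohort's rate. Children well controlled on melatonin would tend not to pass the screen, which requires a current symptom the parent calls a problem; those who do pass might still improve. The 2020 recommendation makes recent prescribed blanket use less likely, although that also makes an uneven spread of prior use more plausible.

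The article is condensed. Its section on patient and public involvement mentions exclusion criteria planned with the clinic, so a fuller protocol may contain a rule on sleep treatment. For that reason the eligibility half of this point is a request to reconcile, not a finding of error. The covariate half does not depend on it, because the article does name its covariates and leaves this one out.

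Finally, the design is openly pragmatic. Making new starters the primary population would change the routine-practice question and is not warranted here. Nor is the problem beyond repair after the data are in: the information needed is collected.

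**Conclusion.** The point holds in a limited form. The displayed eligibility criteria are silent on current or recent melatonin or blanket use and sit uneasily with a baseline defined as before treatment. Recorded prior sleep treatment is a plausible confounder of a preference-based comparison and is absent from the named covariates. The stated use of treatment patterns is confined to the long-term analyses.

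The size of the bias is unknown. If prior users gain nothing further, the 4-point contrast becomes about 2.7 with a one-third share in both arms (82% power at 150 per arm) and 3.0 with a 10% share in the melatonin arm only (90% power). Prior melatonin non-responders in the blanket arm would act in the opposite direction, so even the sign of the net bias cannot be stated. These figures rest on assumed shares, zero further gain and an SD of 8.

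**What to change.** 1. Reconcile the eligibility text with the definition of baseline: say whether children currently or recently using melatonin or a blanket may enter and, if they may, what baseline means for them.
2. From the baseline items, supported by the prescription records, classify each child as a new starter or as a current or recent user of melatonin and/or a blanket. The baseline item covers only the last month, so the records are needed to identify melatonin stopped earlier.
3. Add this variable to the covariates of the 12-month across-arm CSHQ analysis.
4. Prespecify a sensitivity analysis of the same contrast in new starters. The whole cohort stays primary.
5. Count children on both treatments at day 0 as combined use from baseline.

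The cost is wording and some classification work; no new data collection is needed. The downside is a smaller set for the sensitivity analysis: about 100 per arm if one third are prior users, an assumed share. That is still above the 64 per group in the sample-size calculation, though attrition and switching would reduce it further.
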